##### Implementers

As part of the process evaluation, people who have been involved in implementing the intervention are identified by the programme manager and other study team members, as well as by cluster contacts. The study team contact those eligible and provide them with a participant information sheet, allowing adequate time to consider participation and giving people the opportunity to ask questions.

#### Informed consent

##### Who will take informed consent?

Trained and delegated members from teams within clusters or from the study team consent patients and healthcare professionals to participate in the trial or to be contacted for an interview (e.g. if declining trial participation). Completed consent forms are uploaded electronically into a ‘participant record’ on the REMORA2 trial database hosted on REDCap and managed by the study team. A model consent form is publicly available in our trial repository [40].

##### Additional consent provisions for collection and use of participant data and biological specimens

All participants are asked to consent for reuse of their data for future research. Reuse of research data will be at the discretion of the co-principal investigators and will only be granted where adequate data protection measures are in place that ensure data confidentiality. We are not collecting biological specimens in this trial.

#### Participant timeline

Figure 3 shows the time schedule of enrolment, interventions and assessments. Implementation of the intervention (e.g. technical integration of the interactive dashboard into local electronic health record systems, staff training on how to use the dashboard) is completed prior to recruitment commencing, so no further implementation (or washout) time is required at the point of clusters switching over.

**Fig. 3 Fig3:**
[figure not shown]
SPIRIT diagram of schedule of activities. Abbreviations: Brief IPQ: Brief Illness Perception Questionnaire; CDAI: Clinical Disease Activity Index; CollaboRATE: share decision making questionnaire; COM-B: Capabilities, Opportunities, Motivations for Behaviour change questionnaire; DAS28: Disease Activity Score for 28 joints; EQ-5D-5L: EuroQol five-dimension scale questionnaire; HAQ: Health Assessment Questionnaire; PEI: Patient Enablement Instrument; RAID: Rheumatoid Arthritis Impact of Disease score; RAPID-3: Routine Assessment of Patient Index Data 3; WPAI-RA: Work Productivity and Activity Impairment Questionnaire: Rheumatoid Arthritis. **a** Frequency and time points of follow-up appointments are scheduled by the rheumatology team and according to clinical need. No additional visits are mandated as part of the REMORA2 trial. Procedures listed reflect the maximum number of expected activities; **b** Clinical data extracted from the electronic health record at t_0_ comprises data collected at the most recent appointment within the period from 6 months before or 1 month after the time of allocation; **c** For patients who have a clinic visit between months 9 and 12, the REMORA app is deactivated after 12 months. Those who do not have a clinic visit in this period are asked to continue tracking their symptoms beyond 12 months, with the REMORA app being deactivated as soon as they had their final clinic visit; **d** Assessments take place throughout the follow-up phase with participants only being interviewed/observed once; **e** Intervention group only

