*CDAI* Clinical Disease Activity Index for RA, *CollaboRATE* share decision making questionnaire, *COM-B* Capabilities, Opportunities, Motivations for Behaviour change questionnaire, *CRF* Case report form, *DAS28-CRP* Disease Activity Score for 28 joints using C-reactive protein, *EHR* Electronic health record, *EULAR* European Alliance of Associations for Rheumatology, *EQ-5D-5L* EuroQol five-dimension scale questionnaire, *HAQ* Health Assessment Questionnaire, *IPQ* Illness Perception Questionnaire, *PEI* Patient Enablement Instrument, *RA* rheumatoid arthritis, *RAID* Rheumatoid Arthritis Impact of Disease score, *RAPID-3* Routine Assessment of Patient Index Data 3, *SJC28* Swollen Joint Count for 28 joints, *TJC28* Tender Joint Count for 28 joints, *WPAI-RA* Work Productivity and Activity Impairment questionnaire: Rheumatoid Arthritis

^a^For remote consultations, we collected a CDAI score [47] instead of a DAS28 as calculation of the former does not require a blood test

^b^After accounting for measured variables that improve estimate precision, including cluster and outcome assessment at t0 (i.e. baseline); t4 is the time of final follow-up at 12 ± 3 months

^c^Our PPIE group developed a ‘Checking your tender and swollen joints’ section on the study’s website [38] with instructions and a training video for patients on how to self-assess and count tender and swollen joints

^d^Medication use at baseline includes past (i.e. previous 6 months) and current exposures, with any changes to RA medication recorded at all subsequent follow-up visits

^e^Includes number and dates of in-person rheumatology consultations and related travel time/costs, telephone rheumatology consultations, general practitioner consultations and hospital admissions

^f^Related to in-person rheumatology outpatients visits

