##### Electronic health record data extraction

Delegated staff at clusters use an eCRF to enter data extracted from the electronic health record system on clinician-reported disease activity, joint involvement and severity and medication and resource use. For the baseline assessment, this additionally includes patient demographics (gender, date of birth, ethnicity, smoking status, body mass index) and comorbidities.

The baseline assessment is based on information recorded for the clinic visit on, or closest to, the date of recruitment, but within a time window of 6 months prior to or 1 month after consent. Follow-up assessments are performed at each clinic visit during the 12 ± 3-month follow-up window but since these visits are scheduled by the care team as required, no pre-defined schedule of follow-up data extractions has been set.

Healthcare professionals complete paper versions of the eCRFs during follow-up visits to aid data collection.

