##### Primary outcome analysis

The primary analysis will use a generalized linear mixed-effects regression model, with DAS28-CRP at 12 ± 3-months follow-up as the outcome [61, 62]. Model predictors include DAS28-CRP at baseline, follow-up length (in days) and intervention (standard of care or integrated symptom tracking), complemented with further relevant prognostic factors. We will include cluster as a random effect and report the ICC of the linear mixed effects models alongside model coefficients. We will report effect estimates as 95% confidence intervals and consider intervals excluding a null effect as statistically significant. As there is only a single primary outcome of interest, we will not adjust at the type-I error level.

Since our continuous outcome short exposure design means that each participant only receives one intervention, we are not expecting any carry-over effects.

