#### Methods in analysis to handle protocol non-adherence and any statistical methods to handle missing data

We have developed processes and materials to minimize non-adherence and missing data (see ‘Strategies to improve intervention uptake and adherence (i.e. intervention fidelity)’). Where missing data exists, we will summarize and report missingness in terms of outcome, data source (e.g. eCRF, patient web survey) and reasons for missingness (e.g. participant loss-to-follow-up, withdrawal, protocol deviation).

For the primary outcome analysis, we will use multiple imputation by chained equations where data points are assumed to be missing at random. We will detail multiple imputation model specifications in the full statistical analysis plan, but in general, we will seek to impute across all variables included in the primary and secondary analyses; particularly since we expect the primary outcome (DAS28-CRP) to correlate strongly with other, secondary measures of disease severity (e.g. clinical disease activity index [47]).

A sensitivity analysis will replicate the primary outcome analysis using complete case analysis (i.e. using only observed data from the non-imputed final dataset) and we will present its findings alongside those from the primary outcome analysis. Should the study team feel that data may not be missing not at random (e.g. because of unanticipated events), we will revise the statistical analysis plan to include additional analysis strategies for quantifying the robustness of the point estimate generated from the primary analysis model. Any additional sensitivity analyses will be presented in the main REMORA2 trial report.

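### The baseline visit is chosen by date alone, so a remote appointment can leave the baseline DAS28-CRP missing when another visit in the window recorded one

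*Protocol article*

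**What the plan says.** The protocol article states the baseline rule twice.

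- Fig. 3, note b: clinical data extracted from the health record at baseline "comprises data collected at the most recent appointment within the period from 6 months before or 1 month after the time of allocation".
- Electronic health record data extraction: "The baseline assessment is based on information recorded for the clinic visit on, or closest to, the date of recruitment", provided it falls "within a time window of 6 months prior to or 1 month after consent".

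Both rules select a visit by its date. Neither requires that the visit yielded a DAS28-CRP, and neither gives a fallback to another visit in the window.

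Table 1, note a, attached to the primary outcome, says: "For remote consultations, we collected a CDAI score [47] instead of a DAS28 as calculation of the former does not require a blood test". The trial mandates no extra visits, and laboratory values come only from usual care.

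In the Primary outcome analysis section, "Model predictors include DAS28-CRP at baseline"; the definition of the primary outcome also names it as a covariate. On missing data: "For the primary outcome analysis, we will use multiple imputation by chained equations where data points are assumed to be missing at random". A complete-case sensitivity analysis accompanies this.

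**The concern.** Suppose a patient had an in-person visit with a full DAS28-CRP two months before allocation and a telephone appointment one week before it, and was recruited at about the time of allocation. Both rules pick the telephone appointment, which gives a CDAI only. The recorded in-window DAS28-CRP is passed over and the covariate becomes missing.

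Imputation is meant for values that do not exist. Here it would stand in for a value that is in the record. The primary analysis would lose some of the precision that baseline adjustment is meant to bring, and the complete-case analysis would lose the patient altogether.

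The two statements also differ from each other. Suppose the in-person visit was two weeks before allocation and a telephone appointment followed three weeks after it. The nearest-visit rule picks the in-person visit. The most-recent rule, read as the latest appointment in the window, picks the telephone call. Whether this patient has a baseline DAS28-CRP then depends on which sentence the site follows.

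**Working it through.** **1. The plan's own figures.** Inputs from the Sample size section: difference 0.6, SD 1.2, ICC 0.05, cluster auto-correlation 0.8 with discrete time decay, coefficient of variation of cluster size 0.15, 16 clusters in eight steps (nine periods), 27 patients per cluster (3 per cluster-period). Two-sided alpha of 0.05 is assumed. The generalised least squares variance with fixed period effects gives SE = 0.174 and power 93.3%, which agrees with at least 90% at 432 patients. Recruitment: 27/(0.70 × 0.85) = 45.4, rounded up to 46; 46 × 16 = 736. The calculation takes no credit for baseline adjustment and makes no allowance for a missing baseline.

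**2. Precision of the primary analysis.** The documents give neither the baseline-outcome correlation ρ nor the share q of patients without a baseline DAS28-CRP. Assume ρ = 0.5 and q = 0.1 to 0.3, and let the precision scale with the average residual variance, on a scale where the unadjusted variance is 1.

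- With the baseline observed: 1 − ρ² = 0.75.
- Baseline missing, no other information: v = 1.
- Baseline missing, with a proxy that correlates 0.8 with it and relates to the outcome only through it: v = 1 − (0.8 × 0.5)² = 0.84.
- SE ratio = √{[(1 − q) × 0.75 + q × v]/0.75}.

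| q | average variance, v = 1 | SE rise | average variance, v = 0.84 | SE rise |
|---|---|---|---|---|
| 0.1 | 0.775 | 1.7% | 0.759 | 0.6% |
| 0.2 | 0.800 | 3.3% | 0.768 | 1.2% |
| 0.3 | 0.825 | 4.9% | 0.777 | 1.8% |

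Varying ρ with no proxy: at ρ = 0.3 the rise is √(0.919/0.91) to √(0.937/0.91), or 0.5-1.5%. At ρ = 0.6 it is √(0.676/0.64) to √(0.748/0.64), or 2.8-8.1%.

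**3. Against the stated power.** In every case above the average variance stays below 1, the unadjusted value on which the 432 rests. The missing baselines reduce a gain that the sample size calculation never counted.

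**4. Complete-case analysis.** Remove share q from 432 and recompute the power as in step 1:

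| q | N | no baseline credit | ρ = 0.3 | ρ = 0.5 |
|---|---|---|---|---|
| 0.1 | 389 | 91.3% | 93.6% | 96.9% |
| 0.2 | 346 | 88.6% | 91.3% | 95.5% |
| 0.3 | 302 | 85.1% | 88.2% | 93.4% |

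The first power column is too pessimistic, because every patient left in that analysis has a baseline. The 432 also already excludes the 30% expected not to start tracking, whom intention-to-treat keeps: 736 × 0.85 = 626, and 626 × 0.70 = 438 even with 30% of baselines missing. Dilution of the effect by non-starters is a separate matter.

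**5. How much can be recovered.** The Introduction puts visits 3 to 12 months apart, and the window is 7 months long. At 3-monthly visits it holds two or three (7/3 = 2.3); at 12-monthly visits, at most one (7/12 = 0.6). Only patients with a second in-window visit that recorded a DAS28-CRP gain from a better rule, so q in the tables overstates what can be recovered.

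**The case against.** The strongest reply is that this is only a missing fallback, which belongs in the statistical analysis plan or the full operational protocol. That would hold if the article had left baseline selection open. It states the rule twice, and the loss follows from applying it as stated.

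Imputation is the second reply, and much of it stands. The article plans to impute across the variables of the primary and secondary analyses and names the CDAI as a strong correlate. The baseline web survey goes to every participant at allocation and carries further measures of disease activity. The lower range of SE increases is therefore the more plausible one. An imputed value still carries less information than the recorded one.

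Third, the problem may be rare. The word used in the extraction section could mean in-person visits only, and the definition of active disease in supplementary Table S3, not shown, might in practice secure a recent DAS28. Fig. 3, however, speaks of appointments, and Table 1, note e counts telephone rheumatology consultations. The frequency remains unknown.

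A reader might infer three stronger points, which the documents do not support:

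- **That the trial becomes underpowered.** Steps 3 and 4 show otherwise for the primary analysis. Falls below 90% appear only in the complete-case sensitivity analysis, with little or no credit for baseline adjustment.
- **That EULAR response becomes unclassifiable.** The stated aim of imputing across secondary variables would make it derivable, and the details are left to the analysis plan.
- **That the effect estimate is biased.** The rule is the same in both groups, and nothing in the text shows a bias.

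**Conclusion.** The point holds as a modest and avoidable loss of precision caused by a badly stated rule. Followed literally, either version of the rule can turn a recorded in-window DAS28-CRP into a missing covariate, and the two versions disagree on selection and on the anchor date.

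Under an assumed correlation of 0.5 and 10-30% of patients affected, the SE of the primary analysis rises by at most 1.7-4.9%, and by about 0.6-1.8% with a proxy correlating 0.8. The correlation, the share affected and the proxy strength are all assumptions. The recoverable subset is smaller than the share affected and cannot be sized from the document. It is worth correcting because the correction is cheap.

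**What to change.** State one rule, in the same words, in Fig. 3, note b and in the section on electronic health record data extraction:

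- Name one anchor date. Allocation is the natural choice, since follow-up is counted from it.
- Take the baseline DAS28-CRP from the in-window visit nearest the anchor at which it was recorded. Prefer visits on or before allocation, and use a visit in the one-month allowance afterwards only if no earlier one has the measure. Dropping that allowance would itself create missing baselines.
- Apply the same rule to TJC28 and SJC28.
- Keep any CDAI from a nearer visit, and the date of the visit used, as auxiliary variables for the imputation.
- Impute only when no in-window value exists.

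The cost is a sentence in two places and re-extraction from existing records for the affected patients, which needs no patient contact and can be done before the data set is locked. The downside is that some baselines will be older, and components of the baseline may come from different visits. Recording the visit date allows the first to be examined or adjusted for.

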### Outcomes

#### Primary outcome

As shown in Table 1, the primary outcome (to address objective 1) is a difference in the marginal mean disease activity score (DAS) as measured on the DAS28 with C-reactive protein (DAS28-CRP), at 12 ± 3 months follow-up between the standard of care and the integrated symptom tracking groups, after accounting for covariates (including baseline DAS28-CRP, study site, follow-up length and others). The DAS28 is a composite disease activity score that incorporates information about swollen joints, tender joints, acute phase response and global assessment [43]. It is used widely in clinical practice and clinical trials and forms the foundation of internationally accepted treatment response criteria [44]. The DAS28-CRP is a subset of the DAS28, which uses the CRP blood test result to derive the composite score. We opted for CRP rather than erythrocyte sedimentation rate (an alternative blood test for calculating DAS28) based on what was most used by participating hospital sites.

**Table 1 Tab1:** Outcomes per objective, including measurement variables, data collection methods, and analysis metrics

Objective	Outcome	Measurement variable	Data collection method	Analysis metric
**Primary objective**				
1	Clinician-reported disease activity	DAS28-CRP [43]^a^	EHR extraction	Difference in marginal mean DAS28-CRP score at t4 between control and intervention group^b^
**Secondary objectives**				
2a	Treatment response categories	EULAR response categories [44]	Derived from DAS28-CRP	Difference in proportion of participants meeting good/moderate/non-response at t4 between control and intervention group^b^
	Patient-reported disease activity	RAPID-3 [45]	Patient web survey	Difference in RAPID-3 total score at t4 between control and intervention group^b^
		Patient global assessment	Patient web survey	Difference in patient global assessment score at t4 between control and intervention group ^b^
		RAID [46]	Patient web survey	Difference in RAID score at t4 between control and intervention group^b^
		CDAI [47]^c^	Patient web survey	Difference in CDAI score at t4 between control and intervention group^b^
	Joint involvement and severity	TJC28	EHR extraction	Difference in TJC28 score at t4 between control and intervention group^b^
		SJC28	EHR extraction	Difference in SJC28 score at t4 between control and intervention group^b^
	Medication use	n/a	EHR extraction	Difference in medication use of prescribed medication at t4 between control and intervention group^b, d^
	Work impairment	WPAI-RA [48, 49]	Patient web survey	Difference in WPAI-RA score at t4 between control and intervention group^b^
	Quality of life	EQ-5D-5L [50]	Patient web survey	Difference in EQ-5D-5L health profiles, index score and quality-adjusted life years at t4 between control and intervention group^b^
	Disability	HAQ [51]	Patient web survey	Difference in HAQ score at t4 between control and intervention group^b^
2b	Patients’ experience of shared decision-making during clinic visits	CollaboRATE [52]	Patient web survey	Difference in CollaboRATE score at t4 between control and intervention group^b^
	Researcher-observed shared decision-making processes during clinic visits	OPTION5 [53]	Clinic observations	Difference in OPTION score at t4 between control and intervention group^b^
	Patients’ experience of clinic visit quality	PEI [54]	Patient web survey	Difference in PEI score at t4 between control and intervention group^b^
	Patients’ self-management	COM-B [55]	Patient web survey	Difference in COM-B score at t4 between control and intervention group^b^
	Patients’ understanding of their RA	Brief IPQ [56]	Patient web survey	Difference in brief IPQ score at t4 between control and intervention group^b^
	Perceptions of self-management, clinic visits, and decision-making processes	n/a	Interviews with patients and healthcare professionals participating in trial; clinic observations	Comparative thematic and conversation analysis of transcripts between control and intervention group
3	Expectations, experiences and views on the acceptability and usefulness of integrated symptom tracking	n/a	Interviews with patients and healthcare professionals participating in trial or declining participation; interviews with implementers; clinic observations; CRFs; patient web survey	Thematic and conversation analysis of transcripts; descriptive analysis of survey responses and CRFs
	Facilitators and barriers to behaviour change and intervention implementation and uptake	n/a		
4	Quality of life	EQ-5D-5L [50]	Patient web survey	Difference in EQ-5D-5L health profiles, index score and quality-adjusted life years at t4 between control and intervention group^b^
	Duration of consultation	n/a	Clinic observations	Difference in cumulative consultation duration at t4 between control and intervention group^b^
	Medication use	n/a	EHR extraction	Difference in medication use of prescribed medication at t4 between control and intervention group^b, d^
	Resource use^e^	n/a	EHR extraction; patient web survey	Difference in cumulative resource use duration at t4 between control and intervention group^b^
	Patient travel time and costs^f^	n/a	Patient web survey	Difference in cumulative travel time and costs at t4 between control and intervention group^b^
	Healthcare professionals’ engagement with integrated symptom tracking	n/a	Interactive dashboard usage data; CRFs	Descriptive analysis of number and duration of views of interactive dashboard
	Patients’ engagement with integrated symptom tracking	n/a	Symptom completion data	Descriptive analysis of number of completed daily, weekly and monthly questionnaires
5	All outcomes as listed above for objectives 1–4	n/a	n/a	Exploratory analyses of relationships between primary and secondary indicators of disease activity (objectives 1 and 2a) and other secondary outcomes

*CDAI* Clinical Disease Activity Index for RA, *CollaboRATE* share decision making questionnaire, *COM-B* Capabilities, Opportunities, Motivations for Behaviour change questionnaire, *CRF* Case report form, *DAS28-CRP* Disease Activity Score for 28 joints using C-reactive protein, *EHR* Electronic health record, *EULAR* European Alliance of Associations for Rheumatology, *EQ-5D-5L* EuroQol five-dimension scale questionnaire, *HAQ* Health Assessment Questionnaire, *IPQ* Illness Perception Questionnaire, *PEI* Patient Enablement Instrument, *RA* rheumatoid arthritis, *RAID* Rheumatoid Arthritis Impact of Disease score, *RAPID-3* Routine Assessment of Patient Index Data 3, *SJC28* Swollen Joint Count for 28 joints, *TJC28* Tender Joint Count for 28 joints, *WPAI-RA* Work Productivity and Activity Impairment questionnaire: Rheumatoid Arthritis

^a^For remote consultations, we collected a CDAI score [47] instead of a DAS28 as calculation of the former does not require a blood test

^b^After accounting for measured variables that improve estimate precision, including cluster and outcome assessment at t0 (i.e. baseline); t4 is the time of final follow-up at 12 ± 3 months

^c^Our PPIE group developed a ‘Checking your tender and swollen joints’ section on the study’s website [38] with instructions and a training video for patients on how to self-assess and count tender and swollen joints

^d^Medication use at baseline includes past (i.e. previous 6 months) and current exposures, with any changes to RA medication recorded at all subsequent follow-up visits

^e^Includes number and dates of in-person rheumatology consultations and related travel time/costs, telephone rheumatology consultations, general practitioner consultations and hospital admissions

^f^Related to in-person rheumatology outpatients visits

